Participant inclusion criteria are being 18 years or older at the start of the study and having a diagnosis of mild to moderate AUD according to the MINI (2 to 5 MINI AUD symptom criteria) [20], competence to consent and participation, ability to speak and read English, and consistent and reliable access to the internet. Additionally, contemplation about stopping or having stopped consuming alcohol in the past 30 days is required. This will be assessed by the RCQ (participants should be in the contemplation or action stage according to the questionnaire) and by asking them about when they stopped drinking or began considering alcohol cessation [34,35]. Exclusion criteria are acute hypomanic or manic episodes, acute psychosis, other active substance use disorders classified as moderate or severe, active suicidal or homicidal ideation, untreated clinically substantial somatic symptoms or mental disorders, or current enrollment in another relapse prevention program. Additionally, men who consumed more than 4 drinks per day or 14 drinks per week and women who drank 3 drinks per day or 7 drinks per week in the past month will be excluded [36].

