### Procedure

Upon completion of the eligibility assessments, participants will be randomly assigned through a computerized system to one of the 2 groups: e-RPT or face-to-face RPT. Participants will be equally stratified (e-RPT n=30; face-to-face RPT n=30). These treatments will be delivered as an augmentation to treatment as usual (eg, medications, regular physician or clinician visits, referrals, or consultations that are conducted outside of this research study). The e-RPT program will be delivered through the Online Psychotherapy Tool (OPTT), a secure and interactive platform developed by the PI [37]. The face-to-face RPT program will be delivered through videoconference sessions using Microsoft Teams. Participants in the e-RPT and face-to-face groups will also have access to OPTT to access the triage module, the daily drinking diary (Figure 1), and assessment questionnaires.

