### Face-to-Face RPT

Participants in the face-to-face intervention will meet with their therapist weekly through videoconferencing on Microsoft Teams [38]. During these 1-hour sessions, therapists will follow the same 10-week structure and content as e-RPT (Table 1). In contrast to e-RPT, where homework is written web-based by the therapist, the homework for the face-to-face sessions will be reviewed with the participant during the live session. At the end of each session, participants will receive the same homework and feedback as the e-RPT condition.

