### Outcome Measures

The primary objective of this study will be to determine if e-RPT has similar effectiveness to face-to-face RPT at reducing alcohol consumption and preventing relapses. This study defines relapse as either the consumption of at least 2.5 oz. of pure ethanol, which is around 4 and a half standard drinks (Canadian guidelines for standard drinks: 12 oz of beer with 5% ethanol, 12 oz of cider with 5% ethanol, 5 oz of wine with 12% ethanol, and 1.5 oz of spirits with 40% ethanol) [41,42] on one occasion or hospitalization because of alcohol drinking [43]. Therefore, to determine the effectiveness of this program, daily alcohol consumption will be recorded in a drinking diary accessible through OPTT. This diary will ask the participants to report how many drinks they consumed on each day of the week, where they had those drinks, with whom, and if their alcohol consumption resulted in hospitalization (Figure 1).

The study will also determine whether e-RPT and face-to-face RPT have a beneficial effect on self-efficacy, quality of life, resiliency, coping behaviors, and depressive symptomatology. These metrics will be assessed through the following scales: Situational Confidence Questionnaire (SCQ-100) [44], 14-item Resilience Scale (RS-14) [45], Coping Behaviors Inventory (CBI) [46], Patient Health Questionnaire (PHQ-9) [47], and Quality of Life Enjoyment and Satisfaction Questionnaire—Short Form (Q-LES-Q-SF) [48]. These assessment scales will be completed at study entry (baseline), amid the program (week 5), and post treatment (week 10). After the treatment period, we will conduct follow-up assessments with all our outcome measures at 3, 6, and 12 months. The amount of time that e-RPT therapists spend writing feedback compared to the 1-hour face-to-face session will be used as a measure of therapists’ time efficiency and will be tracked on the OPTT platform.

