## Results

According to the literature on the efficacy of face-to-face psychotherapy compared to web-based psychotherapy in the management of AUD, we hypothesize that both e-RPT and face-to-face RPT will reduce alcohol consumption and relapse risk and improve secondary outcome measures (depressive symptomatology, self-efficacy, quality of life, and resilience) [44-47]. Recruitment and data collection are expected to end in October 2023. Data analysis will be concluded by December 2023, at which point the process of knowledge dissemination will begin, including but not limited to peer-reviewed publications, scientific presentations, grant proposals, and reports.

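### With no arm that goes without RPT, the trial cannot determine whether each therapy benefits the five secondary outcomes; it can only compare the two delivery formats

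*Protocol article*

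**What the plan says.** The secondary objective appears in three places. The Objective paragraph of the Abstract and the Introduction speak of assessing the effects of e-RPT, or of online treatment, on the secondary domains. Outcome Measures is the most definite: "The study will also determine whether e-RPT and face-to-face RPT have a beneficial effect on self-efficacy, quality of life, resiliency, coping behaviors, and depressive symptomatology". The subject there is both therapies, so this is a claim about each one and not a contrast between them.

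The Results section gives the matching hypothesis, that "both e-RPT and face-to-face RPT will reduce alcohol consumption and relapse risk and improve secondary outcome measures". The Discussion expects e-RPT to be effective and bases this on earlier validation of face-to-face RPT.

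On design, the Procedure section says that "participants will be randomly assigned through a computerized system to one of the 2 groups: e-RPT or face-to-face RPT", with 30 per arm, and adds: "These treatments will be delivered as an augmentation to treatment as usual". The Face-to-Face RPT section gives that arm the same structure, content, homework and feedback as e-RPT. Under Procedure and Triage Module, both arms complete the same introductory module and use the same drinking diary. On entry, Study Design and Participants says that "contemplation about stopping or having stopped consuming alcohol in the past 30 days is required".

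Data Analysis plans a 2 by 3 repeated measures ANOVA (two arms; weeks 0, 5 and 10), described as testing the effects of the interventions.

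**The concern.** To determine that a therapy is beneficial, one needs to know what would have happened without it. No arm here supplies that. Randomization protects the comparison of e-RPT with live RPT by video, and nothing else.

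Participants enter when they have recently stopped drinking or are considering it, they continue usual care, and they record their drinking daily. Any of these could move confidence, coping, mood or quality of life over ten weeks. If the scales improve in both arms, the data cannot say how much of the change, if any, is due to RPT.

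Finding the arms alike does not settle it, because two therapies that add nothing to usual care would also look alike. This matters because the Discussion foresees uptake by clinics and insurers, who would want to know whether e-RPT works and not only whether the two formats differ.

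**Working it through.** **1. What each ANOVA term estimates**

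| Term | Contrast | Randomized? | What it can show |
|---|---|---|---|
| Arm | e-RPT against live RPT, averaged over weeks 0, 5 and 10 | Yes | Difference between formats |
| Arm by time | Difference in change between the arms | Yes | Difference between formats |
| Time | Change common to both arms | No | Therapy plus everything else that changed |

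Let the mean change in arm *j* be *τ_j + δ*, where *τ_j* is the effect of that therapy and *δ* is the change that would have occurred without it. The arm-by-time term estimates *(τ_e + δ) − (τ_f + δ) = τ_e − τ_f*, so *δ* cancels. The change within an arm estimates *τ_j + δ*, and nothing in the trial estimates *δ* separately. The question under Outcome Measures is whether *τ_e* and *τ_f* are each favourable, and neither is identified. This holds for any value of *δ* and any sample size.

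**2. How easily a zero effect could look like a benefit**

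The documents give no figure for *δ* on the five scales, so this step is an illustration on stated assumptions.

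Inputs from the protocol article: 30 per arm (Procedure); two-sided α = .05 and dropout of up to 40% (Data Analysis). Completers per arm: 30 × 0.6 = 18.

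Assumed inputs: *τ* = 0; *δ* = 0.2, 0.3 or 0.5 SD of the score; correlation between baseline and week 10 *ρ* = 0.5.

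SD of change = SD × √(2(1 − ρ)) = SD × √1 = SD, so the standardized change equals *δ*.

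Paired t test: noncentrality = *δ*√n with n − 1 degrees of freedom. For n = 30 and *δ* = 0.3 this is 0.3 × √30 = 1.64, against a critical value of 2.045, giving a probability of 0.36.

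Probability of a significant change when the therapy effect is zero:

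| Sample | *δ* = 0.2 | *δ* = 0.3 | *δ* = 0.5 |
|---|---|---|---|
| One arm, n = 30 | 19% | 36% | 75% |
| One arm, 18 completers | 13% | 22% | 52% |
| Both arms pooled, n = 60 | 33% | 63% | 97% |

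The rate with *δ* = 0 would be 5%. The objective concerns each therapy, so the one-arm rows are the relevant ones. The pooled row approximates the ANOVA time effect.

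Sensitivity for one arm of 30:
- With *ρ* = 0.3 the SD of change is √1.4 = 1.18 SD, and the probabilities are 15%, 27% and 61%.
- With *ρ* = 0.7 it is √0.6 = 0.77 SD, and they are 28%, 54% and 93%.
- If Bonferroni is applied over five scales (α = .01, an assumption, since the article does not say where it applies), *ρ* = 0.5 gives 6%, 15% and 50%.

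**3. The plan's own figure**

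The article gives no figure on this point. Its only calculation is the sample size of 60, and the point does not depend on it.

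**The case against.** The strongest reply is that this is an active-comparator trial. The Discussion says that face-to-face RPT has been validated and that comparing e-RPT with it strengthens the design. On that reasoning, similarity to a working therapy implies benefit. This is a legitimate route, but it rests on an outside premise that the trial cannot check in its own participants, with research assistants as therapists and sessions held by video. It allows benefit to be inferred under an assumption. It does not let the study determine benefit, and the limitations in the Discussion do not mention it.

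Several stronger readings are tempting but are not supported:

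- *The whole trial is undermined.* It is not. The primary objective compares the two arms and is untouched.
- *The plan commits to declaring benefit from the time effect.* It does not say so. The ANOVA has three terms, and the article does not name the one on which benefit will be judged. The point is that only the time term could bear on each therapy separately.
- *Regression to the mean will inflate the results.* Support for this is weak. Entry sets no threshold on any of the five scales. For drinking, heavier past-month drinkers are excluded, which would push regression towards more drinking.
- *Usual care is unrestricted.* Not entirely, since people enrolled in another relapse prevention program are excluded.
- *Natural recovery is to be expected.* The article's only figures on clinical course are relapse rates of 60% to 80% after 3 months of treatment and 70% to 80% at 12 months, which point to deterioration in drinking. Background change could go either way.
- *The hypotheses in the Results and Discussion are errors.* They may stand as expectations.

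**Conclusion.** The secondary objective, as worded under Outcome Measures, cannot be answered by this design. That conclusion follows from the two-arm structure and needs no numerical assumption. It concerns the five secondary domains only.

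The size is illustrative: 19% to 75% false attribution within an arm of 30, or 13% to 52% with 18 completers, for an assumed background improvement of 0.2 to 0.5 SD at correlation 0.5. The pooled 33% to 97% should not be quoted as the risk for each therapy. If background change were nil, the rate would be the nominal 5%. If it were adverse, the within-arm change would understate benefit. Either way, it could not be read as the therapy effect.

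**What to change.** Four wording changes to the protocol:

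1. **Abstract (Objective), Introduction and Outcome Measures:** restate the secondary objective as the between-arm difference, e-RPT against face-to-face RPT, on each of the five scales, tested by the arm-by-time term over the planned assessments.
2. **Data Analysis:** state that the time effect and within-arm changes will be reported descriptively with confidence intervals and will not be attributed to therapy.
3. **Results and Discussion:** keep the hypotheses, presented as expectations and not as findings the trial can establish.
4. **Discussion, limitations:** add that, without an arm that goes without RPT, any inference that either therapy is beneficial rests on external evidence for face-to-face RPT.

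No change to the arms, assessments or sample size follows from this point. The cost is a weaker stand-alone claim about e-RPT. If that claim is essential to the sponsor, a concurrent arm without RPT would be needed, which would be a different and larger trial.

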**Objective:**

This study protocol aims to establish the first academic e-RPT program to address AUD in the general population. The primary objective of this study is to compare the efficacy of e-RPT to face-to-face RPT in decreasing relapse rates. The secondary objective is to assess the effects of e-RPT on quality of life, self-efficacy, resilience, and depressive symptomatology. The tertiary objective is to evaluate the cost-effectiveness of e-RPT compared to face-to-face RPT.

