Therefore, this study proposes the development, study, and implementation of an e-RPT program for the management of AUD. The proposed program could be a viable solution to address the potential accessibility, stigma, and financial issues presented by traditional in-person therapies [32]. Thus, the primary objective of this study is to compare the efficacy of a secure e-RPT program to face-to-face RPT to decrease relapse rates in patients with AUD. Based on the evidence comparing face-to-face and web-based psychotherapies in other disorders, we hypothesize that both face-to-face RPT and e-RPT will have similar effectiveness in AUD symptom management, reducing alcohol consumption, and lowering relapse rates [33,34]. The secondary objective is to assess the effects of online treatment on quality of life, self-efficacy, resilience, and depressive symptomatology. The tertiary objective is to evaluate cost-effectiveness by comparing the amount of time an e-RPT therapist spends with each patient to the therapists administering face-to-face RPT. The results of this study will supplement the available literature and aid in the development of clinical recommendations for the management of AUD.

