### e-RPT

Participants in the e-RPT group will receive 10 predesigned online modules per week on the OPTT platform. Each module consists of approximately 30 slides and should have an estimated completion time of 45 minutes. At the end of each module, participants will be assigned homework to be completed before their next module is assigned. The therapists will submit personalized feedback by using session-specific therapy feedback templates. These structured templates standardize the quality of feedback across different patients and therapists. In previous studies, therapists have been able to effectively use these templates to prepare feedback in approximately 15-20 minutes [30].

This e-RPT program will focus on teaching essential cognitive and behavioral skills such as identifying maladaptive thought processes, increasing engagement in day-to-day activities, and developing strategies to reduce alcohol consumption. The content of the sessions is outlined in Table 1.

**Table 1 table1:** The program outline and session summary for the 10-week web-based and face-to-face relapse prevention program.

Session number	Session subject
1: Understanding addiction	Introduces relapse prevention and what to expect from the course. The session explains what addiction is, including the symptoms, signs, consequences, and different types of addiction. Participants will create a SMART goal that they will try to achieve throughout the program. They will also share their personal experiences with addiction.
2: Exploring and strengthening your motivation	Focuses on the 5 stages of motivation and the role of motivation in relapse prevention. Helpful techniques are discussed to help them reflect on and boost motivation throughout their recovery journey. Participants will create a pros and cons list about stopping alcohol use and reflect on different aspects of their ability to stop using alcohol.
3: Triggers	Describes what triggers are and how to recognize them, including both internal and external triggers. This session also provides strategies to handle triggers through avoidance and careful planning. Participants will learn to identify their triggers and to be prepared for them if encountered.

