### Training

Therapists for both e-RPT and face-to-face RPT will consist of research assistants who are trained in RPT and writing feedback. All therapists are trained by the PI, who is an expert in the electronic delivery of psychotherapy [30,39,40]. During training, the PI will closely guide the therapists through their first patient (assigning modules, reviewing homework, writing feedback, and conducting face-to-face sessions). All therapists will be supervised by the PI to ensure the quality and reliability of the treatment programs. To ensure the quality of the feedback, therapists will practice writing it using structured templates. All face-to-face sessions and feedback will be reviewed with the PI before being sent to the participants.

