### Data Analysis

The data will be initially assessed for outliers, missing, and nonsensical variables. These variables will not be imputed, since they will be handled as missing. Similar studies that involved CBT and e-CBT demonstrated a dropout rate of up to 40% for both conditions once the study concluded [49]. Thus, this study will intentionally oversample the experimental and control groups to account for this dropout rate. Considering the effect size for face-to-face RPT reported by Harada et al [50] (2021) for CBI (effect size=0.65), a significance level of α=.05 and a power of 0.90, a sample size of 60 (30 per arm) would be sufficient to detect substantial changes from our interventions [51]. As this is the first study aiming to establish an e-RPT program for AUD, this sample size calculation relies on data from face-to-face RPT and takes into account the established effectiveness of online psychotherapy compared to face-to-face psychotherapy [30].

The analysis will begin by examining the data for missing, nonsensical, and outlying variables. The data will then be analyzed on a per-protocol basis, excluding missing data, and with intention-to-treat analysis to assess the clinical effects of the program on participants who dropped out prematurely. All calculations will be done using a 2-tailed significance level of α=.05, except for when a Bonferroni correction is needed. The demographic information of program completers and program dropouts will be compared using independent sample *t* tests to identify possible differences. A 2 by 3 repeated measures ANOVA of the primary (daily drinking and relapse) and secondary (SCQ-100, Q-LES-Q-SF, RS-14, CBI, and PHQ-9) outcomes will be conducted to test for the effects of the interventions (e-RPT or face-to-face RPT) throughout the 10-week treatment (0, 5, and 10-week assessment points). Linear regression (for continuous outcomes) and binomial regression analysis (for categorical outcomes) will be used to identify variables associated with outcome measures. Additionally, OPTT will collect usage statistics (ie, number of logins per day, amount of time spent logged in) and compare them to face-to-face metrics (ie, attendance to weekly 1-hour face-to-face sessions) to determine cost and time savings between the 2 programs. All statistical analyses will be conducted using IBM SPSS Statistics for Mac (version 24; IBM Corp).

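### The tertiary objective is labelled cost-effectiveness but compares therapist time only, against a nominal hour, and its savings analysis sets logins against attendance

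*Protocol article*

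**What the plan says.** The abstract states: "The tertiary objective is to evaluate the cost-effectiveness of e-RPT compared to face-to-face RPT". The Introduction says how this will be done: the study will "evaluate cost-effectiveness by comparing the amount of time an e-RPT therapist spends with each patient" with the time of the therapists who deliver face-to-face RPT.

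Outcome Measures gives the measure: "The amount of time that e-RPT therapists spend writing feedback compared to the 1-hour face-to-face session will be used as a measure". The same sentence names the quantity as time efficiency on the therapists' part and places its tracking on OPTT. The e-RPT section supplies the expected value for one side: in earlier studies "therapists have been able to effectively use these templates to prepare feedback in approximately 15-20 minutes". The other side is the scheduled one-hour session, held by videoconference on Microsoft Teams (Procedure; Face-to-Face RPT). Procedure lists what both groups use OPTT for: the triage module, the drinking diary and the questionnaires. It does not list the timing of live sessions.

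Data Analysis adds a second comparison. OPTT will collect logins per day and time logged in, and the analysis will "compare them to face-to-face metrics (ie, attendance to weekly 1-hour face-to-face sessions) to determine cost and time savings between the 2 programs".

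Two further statements bear on therapist time. In the face-to-face arm, "participants will receive the same homework and feedback as the e-RPT condition". Under Training, "All face-to-face sessions and feedback will be reviewed with the PI before being sent to the participants". Neither the time for that feedback nor the principal investigator's review time is named in the measure.

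**The concern.** Three things do not fit together.

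- **The label.** A cost-effectiveness analysis relates a difference in cost to a difference in outcome. The Introduction defines the objective as a difference in therapist time, with neither a cost nor an outcome in it. This is a stated definition, not a detail left to a fuller document.
- **The time comparison.** One side is tracked minutes of one task. The other is the scheduled length of a session. With the hour taken as given, any mean feedback time below 60 minutes counts as a saving.
- **The savings analysis.** Logins and time logged in, set against session attendance, are in different units. They describe how much participants use each programme, not what therapists put in. No cost saving can be computed from them.

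At stake is what the trial may say about affordability. The Discussion closes by presenting the programme to clinics and insurers as a cheaper resource. The tertiary objective is where the trial's own evidence for that would come from.

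**Working it through.** **Inputs**

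- Expected e-RPT feedback time: 15-20 minutes per module (e-RPT section).
- Face-to-face session: 60 minutes, nominal (Outcome Measures; Face-to-Face RPT).
- Sessions or modules: 10 in each arm.
- Claimed efficiency: 3 to 4 web-based patients for one live session (Discussion).
- Dropout: up to 40% in both conditions (Data Analysis). It is used here only to motivate an assumed attendance of 60%.

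**Step 1. Reproduce the article's own ratio.** Ratio = session minutes / feedback minutes.

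- 60/20 = 3.0 and 60/15 = 4.0.
- Saving per session: 60 - 20 = 40 to 60 - 15 = 45 minutes, or 67-75%.
- Over ten sessions: 400-450 minutes per participant.

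This equals the 3 to 4 in the Discussion, which is credited to earlier work. That statement and the 15-20 minutes share a cited source (reference 30). If feedback takes as long as expected, the trial's measure will return the figure already claimed.

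**Step 2. What is fixed and what is measured.** With the comparator at 60 minutes, the saving per session is 60 minus mean feedback time. It is positive unless feedback averages 60 minutes or more, which is three to four times the expected value. So the direction is nearly certain, while the size depends on the tracked e-RPT minutes.

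**Step 3. Charge only attended face-to-face sessions.** Ratio = (10 × attendance × 60) / (10 × feedback minutes), with all ten e-RPT modules still charged. Attendance is an assumption.

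| Attendance | Face-to-face minutes | Ratio at 20 min | Ratio at 15 min |
|---|---|---|---|
| 100% | 600 | 600/200 = 3.0 | 600/150 = 4.0 |
| 80% | 480 | 480/200 = 2.4 | 480/150 = 3.2 |
| 60% | 360 | 360/200 = 1.8 | 360/150 = 2.4 |

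The 60% row is deliberately one-sided. If e-RPT were also charged for only 60% of its modules, the ratio would return to 360/120 = 3.0 and 360/90 = 4.0.

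**Step 4. Add feedback time to the face-to-face arm.** Assume 15-20 minutes on top of each hour, at full attendance.

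- (600 + 200)/200 = 4.0 and (600 + 150)/150 = 5.0.

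**Step 5. Add review by the principal investigator.** Assume 15 minutes per session in both arms, with no extra face-to-face feedback.

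- Saving = 1 - 35/75 = 53% to 1 - 30/75 = 60%.
- Ratio = 75/35 = 2.1 to 75/30 = 2.5.

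Across these choices the ratio runs from 1.8 to 5. The omissions pull in different directions. Leaving out face-to-face feedback understates the saving, and charging unattended hours overstates it.

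**Step 6. The Data Analysis comparison.** On one side are logins per day and hours logged in; on the other, sessions attended. The article does not say whose logins are meant, but the pairing with attendance implies participants'. No conversion from either quantity to therapist minutes or to money is given. Attendance multiplied by a session length would give therapist time, but logged-in time has no such reading.

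**The case against.** A reader might infer that the saving is set by definition and would appear whatever happened in the trial. The article does not support this. Feedback time is tracked, so the size is an empirical result, and the 15-20 minutes is an expectation from earlier studies, not a planned input.

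A reader might also infer that the face-to-face arm has no variance. That goes too far. Data Analysis uses attendance, and attended sessions times one hour differs between participants. Only the time per attended session is fixed.

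Nor does the text establish that face-to-face feedback is extra work. Homework is reviewed live, and feedback comes at the close of the session, so it may fall within the hour. The Training section speaks of review before feedback is sent, which leaves the matter open. Step 4 is therefore an assumption.

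It can fairly be said, too, that Outcome Measures already calls the measure time efficiency, that the Introduction is open about comparing time, and that no scenario above removes the saving. The Discussion does not rest wider rollout on this measure alone.

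All of that stands, and it limits the point. It does not rescue the cost-effectiveness label, the use of logins against attendance to obtain cost savings, or the comparison of tracked minutes with a scheduled hour.

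**Conclusion.** The objective is mislabelled, and the savings comparison in Data Analysis is invalid for its stated purpose. Both follow from what the article says and rest on no assumption beyond reading the logins as participants'.

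The time comparison is informative but weak. Its comparator is nominal per session, and its direction is all but predetermined at 15-20 minutes against 60. Its size is open, and the ratio moves between 1.8 and 5 with the components charged. Those limits rest on the assumed 60% attendance with all modules charged (low end) and on assumed extra feedback time at full attendance (high end).

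The documents do not support saying that e-RPT saves no therapist time, or that the omissions all favour it. Severity is low: only the tertiary objective is affected, and the primary and secondary analyses are untouched.

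**What to change.** - **Record the same components in both arms.** For every randomised participant, log actual therapist minutes for live sessions, feedback writing and time lost to missed sessions. Count review by the principal investigator in both arms or in neither.
- **Report the difference.** Give mean minutes per randomised participant by arm and the mean difference with a 95% CI, bootstrapped if the times are skewed.
- **Separate engagement from time.** Use logins, logged-in time and attendance as engagement measures only, and drop the derivation of cost and time savings from them in Data Analysis.
- **Rename the objective.** In the abstract and Introduction, call it therapist time per participant. Keep cost-effectiveness for an analysis that joins cost to the difference in outcome.

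The cost is a slight recording burden on therapists, mainly for live sessions, since feedback time is already to be tracked on OPTT, plus wording changes. No extra participants or visits are needed. Session minutes should be logged as they occur, because the article describes no source from which they could be recovered later.
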